### Sample size

We aim to recruit 666 relatives of people with psychosis/BD to accurately test the primary hypothesis that there will be a significant difference (p<0.05) between the trial arms in GHQ-28 at 24-week follow-up. Our feasibility trial^28^ showed a mean difference in GHQ scores between groups at 6 months (controlling for baseline) of 6.59 units (SD 16.6 units) in favour of the REACT arm. To build a degree of protection against pilot results proving optimistic, and to accommodate adaptations to the design of the study and the intervention, we reduce our estimate of the mean difference in this trial from 6.59 to 5.0 units. We retain our estimate of SD of 16.60 from the feasibility study, consistent with other studies using this measure with relatives in EI services^45^ and somewhat higher than those from other mental health or dementia services.^46 47^ Four hundred and sixty-six participants provides 90% power to reject the null hypothesis (p<0.05), with effect size of 5.0 units assuming 30% dropout by 24 weeks. Although dropout was only 17% in our feasibility trial, it is historically higher in online trials.^19^

### Internal pilot

Our trial includes a 9-month internal pilot with the following criteria:GO: 100% or above of anticipated recruitment at 9 months (333+ participants)AMEND: 80%–100% of anticipated recruitment (267–333 participants); review and amend recruitment strategiesSTOP: <80% of target for 9 months (<267 relatives); inform funders who will determine whether to stop trial.

If the SD of GHQ-28 scores at 24-week follow-up at the end of the internal pilot is higher than the estimated 16.6 units, the sample size will be recalculated and recruitment targets increased accordingly. If SD is lower, sample size will remain unchanged. If GHQ-28 retention at 24 weeks is less than 70%, recruitment target will increase to ensure 466 patients will provide sufficient 24-week primary outcome data to test the primary hypothesis.

### Randomisation

Eligible participants will be randomised using a 1:1 ratio to ‘REACT (including RD)+TAU’ versus ‘RD+TAU’ by the CTRC. We will use web-based variable block randomisation in which the unit of randomisation is the relative. We will explore the effect of sociodemographic and caring-related variables; however, without convincing evidence these will have an effect, we have not stratified randomisation.

A second independent randomisation is carried out at CTRC at 24-week follow-up using a randomised factorial design using the same individual block randomisation, with participants randomised to £10 or £20 reward (shopping voucher) and to the reward being conditional or unconditional on completion of measures to determine relative effectiveness and costs for each reward strategy.

### Allocation concealment and blinding

All data are self-reports and predominantly input online by participants. Where data are collected by post, these will be recorded and inputted by the trial manager blind to allocation. Data are uploaded directly to an electronic database at the CTRC. The system only allows valid values to be entered. To prevent any bias in the conduct of the study, the chief investigator [name], trial manager [name] and statistician [name] will be blinded to treatment assignment. Participants, REACT supporters [name], clinical supervisors [name] and technical staff are unblinded.

To minimise unblinding any contact with participants will be prefaced by a reminder not to disclose trial arm. If the trial manager is unblinded, then non-automated reminders and any data entry will be done by another blind team member. Chief Investigator [name] will be unblinded only in the case of a serious adverse event deemed to be study-related to ensure the event is appropriately reported and investigated. All instances of unblinding will be recorded.

### Data management storage and security

All participant trial data are collected through an online system at CTRC and stored on secure servers physically located within access-controlled server rooms and backed up nightly to a separate physical location. All identifiable data are encrypted using a 256-bit encryption algorithm. CTRC servers are subject to penetration testing audits undertaken by the University of Liverpool central IT staff. Website usage data and qualitative data from the REACT group and REACT supporter direct messages are taken from the REACT toolkit hosted on a dedicated virtual private server at Lancaster University. All communication with website users is limited to SSL-protected HTTPS protocol to protect passwords and data in transit over internet.

## Data analysis

A full statistical analysis plan is available at https://figshare.com/account/home#/projects/19975. If normally distributed, scores on the primary and secondary outcomes will be summarised using means and SDs for each arm separately, and will be compared between groups using analysis of covariance, adjusting for baseline score, and including all participations according to the randomisation scheme. If the scores are not normally distributed, the median and IQR will be presented for each randomised group and will be compared using the Mann-Whitney U test. An appropriate transformation (eg, log) will be applied, and analysis of covariance will be applied to data, adjusting for baseline score.

To investigate the relationship between website use and outcome, data will be recorded on baseline covariates (correlated with both website use and outcome) and relevant website use (from participants in both arms). Instrumental variable regression will be implemented to estimate impact of website use on the primary outcome (GHQ-28 at 24 weeks), as well as to test whether the mediator variables actually predict change in outcome. Mediating variables will be examined individually in this exploratory analysis.

To assess the impact of the second randomisation, the number (proportion) of participants providing 24-week follow-up data will be presented and compared using the χ^2^ test (or Fisher’s exact test, if expected counts are <5). The independent impact of intervention group on retention rates will be explored by including intervention group along with value of the reward (or un/conditional nature of the reward) as an explanatory variable in logistic regression.

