#### Primary outcome

The primary outcome is relatives’ distress at 24 weeks assessed using GHQ-28 with Likert scoring.^1–4 31^ GHQ-28 showed sensitivity to change previously^26 28^ and has shown significant associations with important functional outcomes in the general population, including GP visits,^32^ absence from work,^33^ incapacity benefits^34^ and severe adverse health outcomes, including deaths.^35^

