### Missing data analyses

To minimise missing data, participants are required to complete the primary outcome measure (GHQ-28) before completing any other measures. Participants are unable to submit any questionnaire with missing fields, thus avoiding missing data within questionnaires. As much data as possible will be collected about the reasons for missing data, and these will be used to inform the handling of missing data. Participants will be invited to give reasons for not responding to the email reminders.

The baseline characteristics of those who do/do not provide data will be compared to demonstrate whether missing data can be assumed to be missing at random (at least with respect to recorded baseline characteristics). A joint modelling approach (using baseline, 12-week and 24-week outcome data) will be used to assess the impact of missing data at 24 weeks on the conclusions drawn from analysis on primary and secondary efficacy outcomes.

Participants are free to withdraw consent from the trial at any time without providing a reason, although we invite them to tell us why they have withdrawn so that we can take this into consideration in future studies.

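### The primary ANCOVA can use only participants with a 24-week GHQ-28; moving the 12-week scores into the primary model is a cheap way to weaken its missing-data assumption

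*Protocol article*

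**What the plan says.** All places are in the protocol article.

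- **Primary outcome:** "The primary outcome is relatives’ distress at 24 weeks assessed using GHQ-28 with Likert scoring".
- **Data analysis:** if normally distributed, outcome scores are compared between arms by ANCOVA, "adjusting for baseline score, and including all participations according to the randomisation scheme". No imputation and no repeated-measures model is named for this comparison.
- **Secondary outcomes:** GHQ-28 is also collected at 12 weeks.
- **Missing data analyses:** "A joint modelling approach (using baseline, 12-week and 24-week outcome data) will be used to assess the impact of missing data at 24 weeks". Its role is to test whether the primary and secondary efficacy findings hold up. Baseline characteristics of those who do and do not provide data are also compared, and reasons for missing data are collected.
- **Sample size:** "We aim to recruit 666 relatives of people with psychosis/BD"; 466 "participants provides 90% power to reject the null hypothesis (p<0.05), with effect size of 5.0 units assuming 30% dropout by 24 weeks".
- **Internal pilot:** recruitment is raised if 24-week retention is below 70%, so that 466 participants provide the primary outcome.

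**The concern.** An ANCOVA of a single time point needs the outcome at that time point. Unless missing scores are filled in, everyone without a 24-week GHQ-28 drops out of the model. The phrase about including all participants can therefore be read as promising more than the named model delivers.

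The larger matter is which analysis carries the headline result. Complete-case ANCOVA assumes that, given arm and baseline, having a 24-week score is unrelated to what that score would have been. A model that also uses 12-week GHQ-28 lets dropout depend on 12-week distress as well, which is a weaker assumption. The plan has both analyses but gives the primary role to the one with the stronger assumption. The planned comparison of baseline characteristics cannot detect dropout driven by distress at 12 weeks.

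Dropout that differs by arm is plausible here. Participants know their allocation. Only the REACT arm has modules, a forum and supporter messaging, and inactivity reminders are described only for that arm. RD participants are told that they will get the modules after the final follow-up. The Data analysis section itself plans to explore whether intervention group affects retention.

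**Working it through.** **1. The plan's own figures.** Inputs from Sample size and Randomisation: difference 5.0, SD 16.6, p<0.05 (taken as two-sided), power 90%, 1:1 allocation, 30% dropout.

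- Per arm, normal approximation: n = 2(1.960 + 1.282)² × 16.6² / 5.0² = 231.6, so 232 (464 in total). The t-based calculation gives 232.6, so 233 per arm, **466** in total. Reproduced.
- 466 / 0.70 = 665.7, so **666**. Reproduced.
- Power with 233 per arm: 0.90.

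**2. Who is in the primary model.** Without a 24-week score: 666 × 0.30 = 199.8, about 200. With one: 666 × 0.70 = 466.2. At the feasibility trial's 17% dropout, 666 × 0.17 = 113 would be missing. The 466 used for power is the same group, so stated power already reflects the loss.

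**3. Precision from adding 12-week scores (illustrative).** Let n₂ = 233.1 per arm have both scores and n₁ per arm have only the 12-week score. With baseline-adjusted correlation ρ between 12 and 24 weeks, the likelihood-based variance of an arm's 24-week mean is

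v = 16.6² × [ρ² / (n₁ + n₂) + (1 − ρ²) / n₂].

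The documents give neither ρ nor n₁. I assume ρ from 0.4 to 0.8, that 25% to 75% of 24-week non-responders have a 12-week score, that all 24-week completers have one, and that 16.6 is the baseline-adjusted SD.

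- Middle case, ρ = 0.6 and 50%: n₁ = 333 × 0.30 × 0.50 = 49.95. The bracket is 0.36/283.05 + 0.64/233.1 = 0.004018. Effective N = 2/0.004018 = 498; SE = 16.6 × √(2 × 0.004018) = 1.49, against 1.54 for complete cases; power 0.919.
- Across the range: 516 to 616 participants contribute, effective N is 474 to 552, SE 1.53 to 1.41, power 0.906 to 0.943.

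The precision gain is real but small.

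**4. Bias (simulation, assumed inputs).** 333 per arm, about 30% missing at 24 weeks, SD 16.6, GHQ-28 correlations 0.45 to 0.65, true effect −5.0. Loss before 12 weeks is completely random; later loss follows a logistic model in 12-week distress, with the log-odds per SD set separately by arm.

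Bias of complete-case ANCOVA by strength of dependence, one arm against the other:

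| Log-odds per SD | Lost before 12 weeks | Size of bias | Share of 5.0 |
|---|---|---|---|
| 0.8 and 0.8 | 10% | about 0 | 0% |
| 0.6 and 0.4 | 10% | about 0.25 | 5% |
| 0.8 and 0.4 | 10% | about 0.5 | 10% |
| 0.4 and 0 | 20% | about 0.3 | 6% |
| 0.8 and 0 | 20% | about 0.7 | 14% |
| 0.8 and 0 | 10% | about 1.0 | 20% |

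Mean estimates with 0.8 in one arm only, by the share of 24-week non-responders who have a 12-week score:

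| Share with 12-week score | Complete-case, dependence in REACT / RD arm | Using 12-week scores |
|---|---|---|
| about 27% | −5.5 / −4.5 | −5.0 / −5.0 |
| 50% | −5.8 / −4.1 | −4.9 / −5.0 |
| 67% | −6.1 / −3.9 | −5.0 / −5.0 |

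The direction depends on the arm: the effect is overstated if distressed REACT participants leave and understated if distressed RD participants leave. The estimator using 12-week scores stayed near −5.0, with an equal or slightly smaller standard error (for example 1.35 against 1.38). I re-ran the scenarios in the first table and obtained the same pattern.

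**The case against.** **The 12-week data are already used.** A reader might infer that they are thrown away. They are not: the joint model brings them in, and retention by arm is examined by logistic regression. A baseline-adjusted ANCOVA with a pre-stated missing-data check is a conventional plan. This stands, and it reduces the point to which of two planned analyses should be primary.

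**The wording need not be a contradiction.** A reader might infer that the plan claims to model all 666. The phrase can equally mean that participants are analysed in the arm to which they were randomised, and the Sample size and Internal pilot sections are open about 466 providing the outcome. This stands: it is ambiguous wording, not a false claim.

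**How many non-responders gave a 12-week score is unknown.** The documents do not say. Those lost before 12 weeks add no follow-up score under any of these models. This stands, and both the benefit and the bias vary with that share.

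**The bias is a scenario.** It is about 0 when dependence is equal in both arms, and it reaches 20% only with strong dependence in one arm and none in the other. Even then it is below one standard error (about 1.4). This stands: nothing in the documents shows that the primary estimate will be biased.

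**The full SAP is not shown and may settle this.** It may define the analysis set in more detail. But the article itself fixes the primary model and gives the 12-week data a different role, so the point concerns a stated choice, not an omission.

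**Conclusion.** The point holds as a cheap improvement. As written, the primary comparison rests on about 466 of 666 participants at 30% dropout, and any 12-week GHQ-28 from the remaining 200 or so informs only a check on the conclusions. If the check disagrees, the estimate with the stronger missing-data assumption remains the headline.

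For dropout that acts through 12-week distress, the complete-case estimate was materially biased only where that dependence, given baseline, differed by arm. Under the assumed inputs the size runs from about 0, through 5–10% of the 5-point target for a moderate difference, to about 20% for strong dependence in one arm only. It shrinks as fewer non-responders have a 12-week score.

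The documents do not support the stronger reading that the trial loses its stated power or that its primary result is known to be biased by a fifth: 466 gives 90%, and the 20% figure belongs to the most extreme scenario examined.

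**What to change.** - Take the primary estimate as the 24-week contrast from a likelihood-based repeated-measures model of 12- and 24-week GHQ-28, with arm-by-time and baseline-by-time terms and an unstructured covariance, including everyone with any follow-up score. Equivalently, run the planned ANCOVA after multiple imputation that includes 12-week GHQ-28.
- Keep complete-case ANCOVA and the planned joint model as sensitivity analyses.
- Reword the Data analysis section to say that participants are analysed as randomised, which of them contribute data to the primary estimate, and under what missing-data assumption.
- If ANCOVA stays primary, at least state that it is complete-case and what it assumes.

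The cost is protocol and SAP wording and a slightly more complex primary model. No new data are needed, and the target remains the 24-week difference in GHQ-28 points. The change does not repair dropout before 12 weeks or data missing not at random.

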**Methods and analysis:**

This single-blind, parallel, online randomised controlled trial will determine clinical and cost-effectiveness of the Relatives Education And Coping Toolkit (REACT) (including an online resource directory (RD)), compared with RD only, for relatives of people with psychosis or bipolar disorder. Both groups continue to receive treatment as usual. Independent, web-based variable, block, individual randomisation will be used across 666 relatives. Primary outcome is distress at 24 weeks (measured by General Health Questionnaire; GHQ-28) compared between groups using analysis of covariance, adjusting for baseline score. Secondary clinical outcomes are carer well-being and support. Cost-effectiveness analysis will determine cost of a significant unit change (three-point reduction) in the GHQ-28. Costs include offering and supporting the intervention in the REACT arm, relevant healthcare care costs including health professional contacts, medications prescribed and time off (or ability to) work for the relative. Cost utility analysis will be calculated as the marginal cost of changes in quality-adjusted life years, based on EuroQol. We will explore relatives’ beliefs, perceived coping and amount of REACT toolkit use as possible outcome mediators. We have embedded two methodological substudies in the protocol to determine the relative effectiveness of a low-value (£10) versus higher value (£20) incentive, and an unconditional versus conditional incentive, on improving follow-up rates.

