### Study aims and objectives

This randomised controlled trial aims to determine the clinical and cost-effectiveness of the REACT toolkit (which includes an online resource directory (RD)) and treatment as usual (TAU), compared with the RD only and TAU. This comparator was chosen to test the effect of offering REACT as an additional intervention to what relatives are currently able to access.

The objectives are to determine the following:impact of REACT on relatives’ distressimpact of REACT on relatives’ well-being and supportimpact of REACT on hypothesised mediators of change, including relatives’ beliefs, perceived coping and amount of use of REACTcosts associated with delivery and maintenance of REACTincremental cost-effectiveness ratio of REACTkey issues for which relatives seek support.

We have embedded two methodological substudies. The objectives are to determine the effect on follow-up rates of the following:a low-value (£10) versus higher value (£20) incentivean unconditional versus conditional incentive.

The primary hypothesis is that there will be a significant difference (p<0.05) between the two arms of the trial in the General Health Questionnaire (GHQ-28) scores at 24-week follow-up.

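### The primary analysis depends on whether observed GHQ-28 scores look normal, and the non-normal branch prescribes two tests without saying which decides

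*Protocol article*

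**What the plan says.** The abstract (Methods and analysis) states that GHQ-28 at 24 weeks will be "compared between groups using analysis of covariance, adjusting for baseline score". No condition is attached.

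The Data analysis section attaches one. The parametric route opens with "If normally distributed, scores on the primary and secondary outcomes will be summarised using means and SDs for each arm separately", followed by ANCOVA on baseline. The alternative begins "If the scores are not normally distributed, the median and IQR will be presented for each randomised group", and the arms are then to be "compared using the Mann-Whitney U test. An appropriate transformation (eg, log) will be applied, and analysis of covariance", this second analysis being adjusted for baseline.

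The primary hypothesis (Study aims and objectives) is that "there will be a significant difference (p<0.05) between the two arms of the trial" in GHQ-28 at 24 weeks. The Sample size section sizes the trial on a mean difference of 5.0 units with SD 16.60.

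**The concern.** Four features of the rule cause difficulty.

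- The abstract and the Data analysis section differ on whether baseline-adjusted ANCOVA on the raw score is unconditional.
- The condition concerns the distribution of the scores. The ANCOVA assumption concerns the residuals, and with over 200 per arm the adjusted mean difference is not sensitive to moderate non-normality in either.
- The non-normal branch yields two p-values, one unadjusted and rank-based, the other adjusted and on a transformation left open. Nothing ranks them against the single p<0.05 hypothesis.
- Neither fallback yields an adjusted between-arm difference in GHQ-28 points, the scale on which the trial was sized. Medians per arm are in points, but they are descriptive.

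At stake is whether the confirmatory test is known before the outcome data are seen, and whether its result can be read against the 5.0-unit target.

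**Working it through.** **1. The plan's own figure.** Inputs from the Sample size section: difference 5.0, SD 16.6, power 90%, alpha 0.05 (taken as two-sided because the hypothesis has no direction), dropout 30%. Allocation is 1:1 (Randomisation).

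- Normal approximation: n per arm = 2 × (1.960 + 1.282)² × 16.6² / 5² ≈ 231.6, so 232.
- t-test version: 232.6, so 233 per arm and 466 in total.
- Recruitment: 466 / 0.70 = 665.7, so 666.

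Both stated figures reproduce. They correspond to an unadjusted comparison on the points scale.

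**2. What baseline adjustment adds.** The Internal pilot section treats 16.6 as the SD of the 24-week scores, so the residual SD under ANCOVA is 16.6 × √(1 − ρ²), with ρ the baseline correlation (assumed; the article gives none). The standard error is that SD × √(2/233), where √(2/233) = 0.0926.

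- ρ = 0: SE 1.538; 5/1.538 = 3.25; power Φ(3.25 − 1.96) = 90%.
- ρ = 0.3: SE 1.467; 5/1.467 = 3.41; power Φ(1.45) = 93%.
- ρ = 0.5: SE 1.332; 5/1.332 = 3.75; power Φ(1.79) = 96%.

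**3. Simulation of the rule.** 2,000 trials per row, 233 per arm, SD 16.6, scores rounded and clipped to 0-84. Assumptions not in the article: mean 35, the value of ρ, normal or gamma shape, an additive 5-point shift, and log(score + 1) for outcome and baseline. MW is Mann-Whitney. Entries are percentages of trials with p<0.05, except the last column.

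| Shape | ρ | True effect | Raw ANCOVA | Log ANCOVA | MW | Log or MW | Log and MW disagree |
|---|---|---|---|---|---|---|---|
| Normal | 0.3 | 0 | 4.6 | 4.8 | 5.0 | 7.6 | 5.4 |
| Normal | 0.5 | 0 | 5.0 | 5.0 | 4.4 | 7.8 | 6.2 |
| Normal | 0.7 | 0 | 5.1 | 4.2 | 5.0 | 8.2 | 7.2 |
| Gamma | 0.3 | 0 | 4.8 | 4.9 | 4.2 | 6.2 | 3.4 |
| Gamma | 0.5 | 0 | 4.5 | 4.8 | 4.6 | 7.4 | 5.4 |
| Gamma | 0.7 | 0 | 4.4 | 3.9 | 4.2 | 7.2 | 6.2 |
| Normal | 0.3 | 5 | 92.6 | 84.1 | 89.2 | 92.6 | 12.0 |
| Normal | 0.5 | 5 | 96.0 | 90.0 | 89.8 | 95.2 | 10.6 |
| Normal | 0.7 | 5 | 99.7 | 95.9 | 90.1 | 98.1 | 10.2 |
| Gamma | 0.3 | 5 | 92.8 | 98.6 | 93.0 | 98.6 | 5.6 |
| Gamma | 0.5 | 5 | 96.4 | 99.4 | 94.0 | 99.4 | 5.4 |
| Gamma | 0.7 | 5 | 99.6 | 100.0 | 93.6 | 100.0 | 6.4 |

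Raw ANCOVA holds its error rate under both shapes. Which fallback is stronger depends on shape. Further runs under other assumed means, shapes and correlations widen the either-test error rate to 6-10% and the disagreement under a true effect to 5-13%.

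**4. How often the switch is triggered.** The article names no test or threshold. As an illustration, a 5% Shapiro-Wilk check on a clipped normal with SD 16.6 and no treatment effect rejects as follows.

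| Assumed mean | Pooled, n = 466 | By arm, either fails |
|---|---|---|
| 30 | about 100% | 94% |
| 32.5 | 96% | 60% |
| 35 | 65-67% | 28% |
| 40 | 17% | 12% |

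With the gamma shape it rejects in 100% of trials.

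**The case against.** The best defence reads the two sections together. Baseline-adjusted ANCOVA appears in the abstract and in both branches of the Data analysis section, while Mann-Whitney shares a sentence with the medians and IQRs and may be meant only to accompany them. The article points to a full analysis plan that may rank the tests and fix the normality criterion and the transformation. The statistician is blinded to allocation, which limits deliberate selection.

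Part of this stands. The normality criterion is the kind of detail an article leaves to the analysis plan. But the conditional switch and the two fallback analyses are stated in the article itself, and they conflict with its unconditional abstract. Blinding does not determine which p-value counts.

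Four stronger readings are tempting, and the documents do not support them:

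- **That a bounded integer score will almost always fail normality at this sample size.** The rejection rate depends on the 24-week mean, which the article does not give, and no test is named.
- **That the plan inflates type I error as it stands.** Each test alone stays near 5%. The inflation arises only if either p-value may be claimed, which the article neither permits nor excludes.
- **That the fallback abandons baseline adjustment, or fails at a score of zero.** The transformed ANCOVA keeps the adjustment, and log is only an example of a transformation.
- **That the cost-effectiveness analysis loses its points scale.** The Cost-effectiveness paragraph under Data analysis assesses change on GHQ-28 separately, so the cost per three-point reduction can still be calculated.

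Nor would Mann-Whitney leave the trial materially underpowered against its plan: about 88-90% against 90% with near-normal scores. The loss is relative to the adjusted analysis.

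**Conclusion.** The point holds as a fault in how the primary analysis is fixed; the sample size is sound. The article makes an unnecessary data-dependent switch, judged on scores instead of residuals, into a branch with two unranked tests. With near-normal scores and ρ of 0.3 to 0.6, the branch costs power relative to raw-scale ANCOVA (about 93-98% against 88-90% for Mann-Whitney and 84-92% for log ANCOVA). It leaves conflicting significance in roughly 5-13% of trials with a true effect, and a type I error of 6-10% if either result may be claimed. These sizes rest on assumed means, correlations and shapes. The two p-values and the loss of an adjusted difference in points arise only if the non-normal branch is entered, and how often that would be is uncertain (17% to 100% in the pooled illustration). This should be fixed; it does not invalidate the design.

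**What to change.** In the Data analysis section, state one primary analysis whatever the distribution: ANCOVA of untransformed 24-week GHQ-28 on arm and baseline GHQ-28, reported as an adjusted mean difference with 95% CI. Check the residuals, and give robust or bootstrap standard errors as a sensitivity analysis. Keep Mann-Whitney and transformed-scale analyses only as labelled sensitivity analyses. Apply the same rule to CWS and to 12-week GHQ-28, and make the analysis plan match.

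This agrees with the abstract, keeps the result on the scale of the 5.0-unit target and leaves 466 and 666 unchanged. The cost is a wording change, made before unblinding. With strongly skewed scores some power may be forgone relative to a log model: in the gamma rows, 92.8% against 98.6% at ρ = 0.3, narrowing at higher correlations.

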### Data collection

Baseline measures including demographic information, outcomes and mediators are completed before randomisation. Demographic data collected include age, gender, ethnicity, marital status, education, employment, living arrangements (including dependents), primary diagnosis of service user, length of time in caring role, number of people caring for, relationship to person(s) with mental health problem, whether or not they live with the person(s), level and type of contact, whether or not they are receiving support from NHS services and internet access.

Twelve and 24 weeks after randomisation, all participants are sent an email reminder to complete the follow-up measures. At 24 weeks, the email content will vary depending on whether participants have been randomised to either £10 or £20 reward and to the reward being conditional (ie, dependent on completion of follow-up questionnaires) or unconditional (ie, offered with the initial request for follow-up data).

To maximise follow-up at the primary outcome point we will:only randomise participants once baseline assessment measures are completedinclude detailed explanations in our recruitment materials to explain to participants why data completion at follow-up is so importantrequire email, telephone and postal contact details at registration so we have multiple methods of contact for follow-upsend participants up to three automated email reminders at 5-day intervals, followed by text, telephone and/or postal requestsincentivise completion of follow-up measures by paying participants shopping voucher(s) at each time point.

To increase overall acceptability and participation rates, we will inform RD participants that they will be able to access toolkit modules after the final follow-up.

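### The incentive comparison is an unadjusted chi-square test that leaves out 12-week completion, a covariate known before the second randomisation, at a plausible cost in power

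*Protocol article*

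**What the plan says.** The abstract and Study aims and objectives give the incentive work two separate aims for follow-up rates: "a low-value (£10) versus higher value (£20) incentive" and "an unconditional versus conditional incentive".

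Randomisation sets the design: "A second independent randomisation is carried out at CTRC at 24-week follow-up using a randomised factorial design". Its purpose there is "to determine relative effectiveness and costs for each reward strategy".

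Data analysis names the comparison: "the number (proportion) of participants providing 24-week follow-up data will be presented and compared using the χ^2^ test", with Fisher's exact test for small expected counts. It does not say whether proportions are compared by margin (£10 v £20; conditional v unconditional) or across the four cells. The next sentence explores the effect of trial arm on retention "by including intervention group along with value of the reward (or un/conditional nature of the reward) as an explanatory variable in logistic regression". No covariate is named for the incentive comparison itself.

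Data collection gives the timing: "Twelve and 24 weeks after randomisation, all participants are sent an email reminder to complete the follow-up measures". Whether a participant responded at 12 weeks is therefore on file before the 24-week allocation is made.

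**The concern.** A participant who answered at 12 weeks is plausibly much more likely to answer at 24 weeks than one who did not. That status is fixed before the voucher allocation, so adjusting for it is legitimate and needs no new data. The article already applies the same principle to its clinical outcomes, which are adjusted for baseline score. An unadjusted test of two proportions ignores this information.

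What is at stake is power in a methodological substudy for which the article states no sample size of its own. Its numbers are inherited from the main trial, so power for a modest voucher effect is limited from the outset. A gain that costs nothing is worth taking.

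**Working it through.** **The plan's own figures.** Sample size gives a difference of 5.0, SD 16.60, 90% power and 30% dropout. Taking a two-sided 5% test, n per arm = 2(1.960 + 1.282)² × 16.6² / 5² = 231.6, so 232 per arm and 464 in total. The article says 466, and 233 per arm gives 90.2% power. 466 / 0.70 = 665.7, so 666. The figures reproduce.

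**Substudy inputs.** From the article: 666 participants and 70% expected retention. Assumed: all 666 are re-randomised and split equally (333 per level of each factor, about 166.5 per cell), with a two-sided 5% test.

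**Power of the stated test, by margin.** Power = Φ{[d − 1.96 √(2 × 0.7 × 0.3 / 333)] / √[(p₁q₁ + p₂q₂) / 333]}, centred on 70%.
- d = 0.10 (65% v 75%): (0.10 − 0.0696) / 0.0353 = 0.861, power 80.5%.
- d = 0.08 (66% v 74%): (0.08 − 0.0696) / 0.0354 = 0.294, power 61.6%.
- The smallest difference with 80% power is 9.9 points.

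**Gain from 12-week completion.** Simulation, 3,000 runs of 666, assuming 75% complete at 12 weeks. Both scenarios keep overall retention at 70%: 0.75 × 0.80 + 0.25 × 0.40 = 0.70, and 0.75 × 0.85 + 0.25 × 0.25 = 0.70. The voucher effect is constant on the logit scale and set to give the stated risk difference. The other factor has no effect in these rows.

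| 24-week response, 12-week completers v non-completers | True difference | Chi-square | Logistic, both factors | Logistic, both factors + 12-week completion |
|---|---|---|---|---|
| 80% v 40% | 0 | 5.0% | 5.0% | 4.6% |
| 80% v 40% | 8 points | 62.0% | 62.0% | 69.0% |
| 80% v 40% | 10 points | 79.9% | 79.9% | 86.5% |
| 85% v 25% | 0 | 4.6% | 4.6% | 4.7% |
| 85% v 25% | 8 points | 61.6% | 61.6% | 78.5% |
| 85% v 25% | 10 points | 80.0% | 80.1% | 92.5% |

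The Monte Carlo standard error near 80% is √(0.8 × 0.2 / 3000) = 0.7 points. The simulated models did not include trial arm.

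With a true 10-point effect of the second factor as well, chi-square v both-factor power was 80.0% v 80.3% and 81.4% v 81.5%. Adding 12-week completion gave 85.7% and 93.1%. Entering both factors therefore gains essentially nothing, and the gain comes from the covariate.

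Repeating the simulation with retention at or slightly below 70% gave 61–64% rising to 67–79% at 8 points, and about 81% rising to 86–93% at 10 points. Across the runs the gain is about 6 to 17 points of power at an 8-point difference and about 5 to 13 at a 10-point difference.

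**Interaction.** The standard error of the difference in risk differences is √(4 × 0.7 × 0.3 / 166.5) = 0.0710. Power is Φ(0.10 / 0.0710 − 1.96) = 29% for 10 points and Φ(0.15 / 0.0710 − 1.96) = 56% for 15 points. For 80% power the true value must be (1.960 + 0.842) × 0.0710 = 0.199, about 20 points.

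**The case against.** The stated objectives are two main effects. Comparing margins of a balanced randomised factorial answers them without bias and with correct type I error. That stands in full.

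A reader might infer from the word 'or' in the logistic sentence that the factorial is analysed wrongly and that one factor at a time wastes power. The documents do not support this. That model serves to explore the effect of trial arm on retention, and it is itself adjusted for one reward factor. The simulated power is the same whether one factor or both are in the model.

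A reader might also infer that the plan would hide a £20 effect confined to conditional payment, so that the wrong strategy is recommended. That goes too far. No interaction objective is stated, and the article does not rule out presenting the four cells. An interaction test at this size would usually be inconclusive.

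The full analysis plan is cited but not shown, and it may name covariates. Silence on such detail would be no finding. The point here is narrower: the article does name the test, and a better one is available from data already collected.

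Finally, the prediction strengths are not in the documents. That also stands. If 12-week completion predicted nothing, the gain would vanish. Withdrawals before week 24 would reduce the 333 per level.

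**Conclusion.** The point holds as a low-severity matter of efficiency. The stated incentive comparison is sound but ignores a pre-randomisation covariate that plausibly predicts the outcome. The avoidable loss is about 5 to 13 points of power at a 10-point difference and about 6 to 17 at an 8-point difference. This assumes 75–78% completion at 12 weeks, 24-week response between 80% v 40% and 84–85% v 20–25%, and an equal split of all 666. There is no bias and no excess type I error, and the primary analysis is unaffected.

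A smaller reporting point goes with it. Because Randomisation speaks of effectiveness and costs for each strategy, the four cells need to be shown. The voucher cost per completer of an unconditional reward depends on that cell's own retention. At an illustrative 70%, a £10 voucher costs £10 / 0.70 = £14.29 per completer if unconditional and £10 if conditional.

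**What to change.** - Make the main incentive analysis one logistic model for 24-week completion, with value, conditionality, trial arm and 12-week completion (yes/no, fixed at the date of the second randomisation).
- Report each main effect as a marginal risk difference with a confidence interval, so that results stay on the retention scale.
- Keep the chi-square or Fisher tests as descriptive, and say that they compare margins.
- Report retention in the four cells with confidence intervals, and the value-by-conditionality interaction as exploratory only. State its power: about 29% for a 10-point and 56% for a 15-point difference in differences.

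The cost is a change of wording in the analysis plan, made before the 24-week completion data are examined by incentive group. All the variables are already collected.
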